**Figure 1 F1:**
[figure not shown]
Procedure timeline for experimental protocol. **(A)** RICE group (RIC with exercise); **(B)** Control group (Sham-RIC with exercise).

Early RIC combined with follow-up exercise training is a novel early rehabilitation model for acute stroke patients; therefore, we set the duration of RIC and exercise (RICE) rehabilitation to be 14 days according to the protocol of “A Very Early Rehabilitation Trial” (AVERT) (13), the well-known and evidence-based clinical study on early rehabilitation of stroke, and our previous study (14).

### Outcomes

#### Primary Outcome

The primary outcome is safety, including any serious RIC-related and exercise-related adverse events. Other safety outcomes include clinical deterioration, recurrence of stroke, fall, angina, myocardial infarction, deep venous thrombosis, pulmonary embolism, pressure sore, chest infection, urinary tract infection, and depression during hospitalization. All adverse events will be determined independently by specially trained members of the same research group who will be blinded to the randomization. Source data will be reviewed if necessary.

#### Secondary Outcomes

There will be two classes of secondary outcomes. (1) Clinical efficacy as determined by the mRS (mRS 0–2 was defined as a favorable prognosis and mRS 3–6 points as a poor prognosis), NIHSS score, Barthel scale, and the proportion of patients achieving independent walking after 90 days (Holden functional classification of walking). (2) Brain infarct volume as determined by MRI diffusion-weighted imaging technique, with the lesion profile plotted at each individual level by an image tool on the workstation to calculate the area. The levels will be multiplied by the thickness of each level and summed to calculate the infarct volume. The calculations will be performed by personnel blinded to clinical data and randomization at baseline and at day 12 ± 2.

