## Methods

### Study Design

This is a single-center, double-blinded, randomized controlled trial that will enroll acute ischemic stroke patients within 24 h of the ischemic event or symptom exacerbation. All participants will be informed about the clinical study and the requirement to give informed consent. The study protocol and informed consent were approved by the regional ethics committee and have been registered with the Clinicaltrials.gov (ChiCTR2000041042).

After receiving informed consent, all enrolled patients will be randomly assigned to either the intervention group (RIC with exercise rehabilitation) or the control group (sham RIC with exercise rehabilitation) at a ratio of 1:1, with 20 patients in each group. Within 24 h of the ischemic event or symptom exacerbation, the groups will start either RIC or sham RIC in 45-min sessions, once a day, for 14 days. All patients will begin exercise rehabilitation training 4 days after the ischemic stroke event in 30-min sessions, twice a day, for 11 days. Brain imaging with MRI will be performed on the day of the stroke for a baseline and again at 12 days. Evidence of stroke severity and disability will be evaluated using the National Institutes of Health Stroke Scale (NIHSS) score and the Barthel Index, which will be administered by trained investigators blinded to the treatment assignment on the day of the stroke for a baseline and at 1, 3, 7, and 90 days after enrollment. Furthermore, the Modified Rankin Scale (mRS) will be administered, and walking ability will be assessed at 90 days.

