### Sample Size Estimation

This is a phase 1 safety and feasibility trial. There are no data available for reference because no clinical study of RIC and exercise therapy in patients with confirmed acute ischemic stroke (mRS ≤ 2, NIHSS score 6–16) has yet been completed. Hertzog (27) has suggested that 10–20 patients in each group are sufficient to assess the feasibility of a pilot study, while Dobkin (28) has shown that 15 patients in each group are usually enough to decide whether a larger multicenter trial should be conducted. A similar number of samples was selected in two other related protocols (29) (Lv et al., Frontiers in Neurology in press ). We therefore set our recruitment goal to 20 patients per group in the present study. The results of this study will be used to determine the safety and feasibility of RICE and be used to estimate the sample size and perform power calculations necessary to plan the phase 2 trials.

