### Statistical Analysis

All statistical analyses will be performed using the statistical software SAS (version 9.1.3; SAS Institute, Cary, NC). Outcome event analyses will be based on the intention-to-treat (ITT) principle, including all randomly enrolled subjects. Subjects' baseline categorical variables will be recorded in percentages (%), and continuous variables will be recorded as means and standard deviations or medians and interquartile ranges. The comparison of baseline parameters of the study subjects will be performed with the Pearson chi-square test and either the *t*-test or the Wilcoxon rank sum test for the categorical and continuous variables, respectively.

The distribution difference of the 90-day mRS scores between the two groups will be evaluated using the common ratio. The public odds ratio of the mRS scores on the 90th day will be evaluated by the sequential logistic regression model. The ratios between the mRS categories (0–2 and 3–6) and adverse events will be estimated with the improved Poisson regression. Infarct volume and β coefficient of the NIHSS score will be estimated by multiple linear regressions. Efficacy assessment will be adjusted based on age, gender, NIHSS baseline score, baseline condition, stroke subtype, intravenous alteplase treatment, and mechanical thrombectomy. The homogeneous dominance ratio of each subgroup will be analyzed *via* the Breslow–Day test to analyze the functional independence of the subgroup for 90 days. The significance level will be set at 0.05 for all tests.

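### The graded day-90 walking scale is summarised only as a proportion walking independently; adding a full-scale analysis would be a small, cheap gain for this secondary outcome

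*Protocol article*

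**What the plan says.** Under Secondary Outcomes, the protocol article lists walking with the mRS, NIHSS and Barthel scale as measures of clinical efficacy, and defines it as "the proportion of patients achieving independent walking after 90 days (Holden functional classification of walking". Study Design says only that "walking ability will be assessed at 90 days", without naming a scale or a summary measure.

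Under Statistical Analysis, the mRS is handled twice. On its ordinal scale, "The public odds ratio of the mRS scores on the 90th day will be evaluated by the sequential logistic regression model". It is also split at 0–2 against 3–6 and analysed by modified Poisson regression. No model is named for walking.

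On the standing of the outcome: "The primary outcome is safety, including any serious RIC-related and exercise-related adverse events", and walking belongs to the first of two classes of secondary outcome. The sample size is 20 per group, and the results are to "be used to estimate the sample size and perform power calculations necessary to plan the phase 2 trials".

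**The concern.** A graded walking classification records degrees of walking ability, and a single cut keeps only which side of the threshold each patient falls on. Two patients with different grades on the same side count as equal. The training described under Interventions includes walking with or without assistance, so differences short of full independence are a plausible place for an effect to appear.

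The article already accepts for the mRS that an ordinal scale deserves an ordinal analysis beside the cut, and gives no reason for treating walking differently. With 40 patients, the loss makes the walking comparison less precise than the grades would allow. That matters only so far as the estimate feeds into phase 2 planning.

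**Working it through.** **Inputs from the document.** 20 per group, 1:1; significance level 0.05 (two-sided assumed, since sidedness is not stated). The sample size follows a pilot rule, "10–20 patients in each group are sufficient to assess the feasibility of a pilot study". It rests on no effect size, event rate or power, so there is no power figure to reproduce; 20 does fit the rule.

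**Assumptions not in the document.** Six grades; independent = top two grades; proportional-odds shift; the control distributions below.

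**1. Precision of the proportion.** The 95% CI half-width for a difference is 1.96 × √(2p(1−p)/20). At p = 0.5 this is 1.96 × √0.025 = 0.31; at p = 0.3 or 0.7 it is 1.96 × √0.021 = 0.28. A binary comparison reaches 80% power only for differences of about 0.43 (control rate 0.3), 0.42 (0.4), 0.40 (0.5) and 0.36 (0.6).

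**2. Information kept by the cut.** Under proportional odds, information is proportional to 1 − Σp̄³, where p̄ is the mean category probability over the two groups. Relative efficiency is the binary value divided by the ordinal value.

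Example, flat control (1/6 per grade), odds ratio 3:
- Control cumulative odds 0.2, 0.5, 1, 2, 5, divided by 3, give treated cumulative probabilities 0.0625, 0.1429, 0.25, 0.40, 0.625.
- Mean category probabilities: 0.115, 0.124, 0.137, 0.158, 0.196, 0.271. Ordinal: 1 − 0.037 = 0.963.
- Mean proportion independent: 0.467. Binary: 1 − 0.467³ − 0.533³ = 0.747.
- Relative efficiency: 0.747 / 0.963 = 0.78.

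**3. Power, Wilcoxon rank-sum on the grades against an uncorrected two-proportion test on the cut** (3,000 simulated trials per row; simulation standard error about 0.9 points at a power near 45%). Control distributions, lowest to highest grade: flat, 1/6 each; U-shaped, 25/10/10/10/15/30%; high, 10/8/10/12/20/40%; low, 30/20/15/12/13/10%.

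| Control | Odds ratio | Independent, control → treated | Full scale | Cut | Gap (points) | Relative efficiency |
|---|---|---|---|---|---|---|
| Flat | 2 | 33% → 50% | 23.2% | 17.2% | 6.0 | 0.75 |
| Flat | 3 | 33% → 60% | 47.0% | 36.8% | 10.2 | 0.78 |
| Flat | 4 | 33% → 67% | 67.9% | 55.0% | 12.9 | 0.78 |
| U-shaped | 2 | 45% → 62% | 21.1% | 16.2% | 4.9 | 0.80 |
| U-shaped | 3 | 45% → 71% | 44.6% | 36.3% | 8.3 | 0.80 |
| U-shaped | 4 | 45% → 77% | 62.6% | 54.3% | 8.3 | 0.80 |
| High | 2 | 60% → 75% | 20.6% | 17.4% | 3.2 | 0.75 |
| High | 3 | 60% → 82% | 43.4% | 33.2% | 10.2 | 0.74 |
| High | 4 | 60% → 86% | 60.3% | 47.2% | 13.1 | 0.73 |
| Low | 2 | 23% → 37% | 23.1% | 17.9% | 5.2 | 0.65 |
| Low | 3 | 23% → 47% | 48.1% | 36.2% | 11.9 | 0.70 |
| Low | 4 | 23% → 54% | 67.5% | 54.1% | 13.4 | 0.73 |

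Relative efficiency is 0.65–0.80, a loss of 20–35%, comparable to 0.20 × 40 = 8 to 0.35 × 40 = 14 patients. Moving the cut to the top one or top three grades widens the range to 0.38–0.91.

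**4. Other control rates, odds ratio 3.** A second set gives 48% against 37% (control rate 30%), 46/37 (45%), 44/35 (60%), 41/28 (70%) and 33/19 (80%): gaps of 9–14 points. A third set gives 36–50% against 19–38%, with gaps up to 17. The widest gaps occur where most controls already walk independently; there the information loss exceeds 35%. At an odds ratio of 2, the second set gives gaps of 2–7 points.

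**5. Effect only at the threshold.** Illustration (assumed): control 10/10/15/30/20/15%, with 25 points moved from the fourth grade to the fifth.
- The cut sees 35% against 60%. By simulation its power is about 33%.
- The rank test sees a probability of a better grade of 0.5 + 0.25 × (0.30 + 0.20)/2 = 0.5625. Its standard error with ties is about 0.090, so z = 0.0625/0.090 = 0.69 and power is about 11%.

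Here the ordering reverses: 11% for the full scale, 33% for the cut.

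**6. Adjustment.** Efficacy assessment is to be adjusted for seven covariates. With treatment, that is at least eight coefficients, or 40/8 = 5 patients per coefficient, before the five intercepts of a six-grade model. The powers above are for unadjusted tests and do not carry over to that model.

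**The case against.** The strongest reply is that nothing here is an error. Independent walking is a legitimate, readable endpoint, the trial is a safety and feasibility pilot, and its size was not set by power. That stands, and it makes this an improvement, not a defect.

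A reader might infer that the plan commits walking to a binary test and rules out anything else. The article does not support that. Statistical Analysis names no walking model, and none for the Barthel scale either, so the article may be condensing and an analysis plan that is not shown may add one. What the article does fix is the outcome definition, which is the proportion alone.

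A reader might also infer that the grades are lost. Walking ability is to be assessed by a graded classification, so the grades may well be recorded and available. The number of grades and the cut-point are not stated; six grades with the top two independent is an outside assumption.

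Finally, the scenarios showing a gain use proportional odds, which favours an ordinal analysis. The threshold-only case shows that the gain is conditional, so the proportion should be kept as an estimated result.

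**Conclusion.** The point holds as a minor efficiency gain. The outcome definition reduces a graded scale to one cut, while the mRS receives both treatments. For an effect spread across grades, the cost is about 20–35% of the information at control independent-walking rates of 23–60%. In power this is about 2–7 points at an odds ratio of 2 and roughly 9–17 at 3, the upper end belonging to higher control rates. All of this rests on the assumed grades, cut and distributions.

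Two stronger conclusions are not supported. Walking is not a main outcome: it is one of four clinical measures among the secondary outcomes. Nor would the full scale make the comparison well powered: the highest figure in the table is 67.9%, at an odds ratio of 4. No document says that phase 2 will be sized on walking, so the benefit there is possible, not certain. The safety aim is unaffected.

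**What to change.** In Secondary Outcomes, define the day-90 Holden grade as a walking outcome beside the proportion, and state which grades count as independent. In Statistical Analysis, add one sentence: the grade will be compared on its full scale by the Wilcoxon rank-sum test, or by a proportional-odds common odds ratio with its 95% CI, unadjusted or with very few covariates given 40 patients. Show the grade distribution by group, and report the independent-walking proportion with its 95% CI alongside.

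The cost is a sentence or two, with no new visits or patients, provided the grade itself is recorded. The downside is small: a common odds ratio is harder to read than a proportion and assumes a roughly uniform shift across grades. The grade distribution and the proportion let the reader judge that assumption.

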### Sample Size Estimation

This is a phase 1 safety and feasibility trial. There are no data available for reference because no clinical study of RIC and exercise therapy in patients with confirmed acute ischemic stroke (mRS ≤ 2, NIHSS score 6–16) has yet been completed. Hertzog (27) has suggested that 10–20 patients in each group are sufficient to assess the feasibility of a pilot study, while Dobkin (28) has shown that 15 patients in each group are usually enough to decide whether a larger multicenter trial should be conducted. A similar number of samples was selected in two other related protocols (29) (Lv et al., Frontiers in Neurology in press ). We therefore set our recruitment goal to 20 patients per group in the present study. The results of this study will be used to determine the safety and feasibility of RICE and be used to estimate the sample size and perform power calculations necessary to plan the phase 2 trials.

### Statistical Analysis

All statistical analyses will be performed using the statistical software SAS (version 9.1.3; SAS Institute, Cary, NC). Outcome event analyses will be based on the intention-to-treat (ITT) principle, including all randomly enrolled subjects. Subjects' baseline categorical variables will be recorded in percentages (%), and continuous variables will be recorded as means and standard deviations or medians and interquartile ranges. The comparison of baseline parameters of the study subjects will be performed with the Pearson chi-square test and either the *t*-test or the Wilcoxon rank sum test for the categorical and continuous variables, respectively.

The distribution difference of the 90-day mRS scores between the two groups will be evaluated using the common ratio. The public odds ratio of the mRS scores on the 90th day will be evaluated by the sequential logistic regression model. The ratios between the mRS categories (0–2 and 3–6) and adverse events will be estimated with the improved Poisson regression. Infarct volume and β coefficient of the NIHSS score will be estimated by multiple linear regressions. Efficacy assessment will be adjusted based on age, gender, NIHSS baseline score, baseline condition, stroke subtype, intravenous alteplase treatment, and mechanical thrombectomy. The homogeneous dominance ratio of each subgroup will be analyzed *via* the Breslow–Day test to analyze the functional independence of the subgroup for 90 days. The significance level will be set at 0.05 for all tests.

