## Abstract

**Objective:** Exercise rehabilitation is an effective therapy in reducing the disability rate after stroke and should be carried out as early as possible. However, very early rehabilitation exercise exacerbates brain injury and is difficult to conduct in stroke patients due to their weakened and potentially disabled state. It is valuable to explore additional early rehabilitation strategies. Remote Ischemic Conditioning (RIC) is a novel therapy designed to protect vital organs from severe lethal ischemic injury by transient sublethal blood flow to non-vital organs, including the distal limbs, in order to induce endogenous protection. RIC has previously been conducted post-stroke for neuroprotection. However, whether combined early RIC and exercise (RICE) therapy enhances stroke rehabilitation remains to be determined.

**Methods:** This is a single-center, double-blinded, randomized controlled trial that will enroll acute ischemic stroke patients within 24 h of symptom onset or symptom exacerbation. All enrolled patients will be randomly assigned to either the RICE group (exercise with RIC) or the control group (exercise with sham RIC) at a ratio of 1:1, with 20 patients in each group. Both groups will receive RIC or sham RIC within 24 h after stroke onset or symptom exacerbation, once a day, for 14 days. All patients will begin exercise training on the fourth day, twice a day, for 11 days. Their neurological function [Modified Rankin Scale (mRS) score, National Institutes of Health Stroke Scale (NIHSS) score, Barthel Index, and walking ability], infarct volume (nuclear magnetic resonance, MRI), and adverse events will be evaluated at different time points in their post-stroke care.

**Results:** The primary outcome is safety, measured by the incidence of any serious RICE-related adverse events and decreased adverse events during hospitalization. The secondary outcome is a favorable prognosis within 90 days (mRS score < 2), determined by improvements in the mRS score, NIHSS score, Barthel Index, walking ability after 90 days, and infarct volume after 12 ± 2 days.

**Conclusion:** This study is a prospective randomized controlled trial to determine the rehabilitative effect of early RIC followed by exercise on patients with acute ischemic stroke.

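### The one analysis named for adverse events, a modified Poisson ratio, has no usable value when an arm of 20 has no events; at assumed rates below about 6% per arm that is the likelier result for the primary outcome

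*Protocol article*

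**What the plan says.** Under Primary Outcome: "The primary outcome is safety, including any serious RIC-related and exercise-related adverse events". The Abstract frames the same outcome as "the incidence of any serious RICE-related adverse events and decreased adverse events during hospitalization". The Primary Outcome section then lists further safety outcomes during the hospital stay, among them falls, infections, recurrent stroke and depression.

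Under Statistical Analysis, the only sentence that gives a method for adverse events is: "The ratios between the mRS categories (0–2 and 3–6) and adverse events will be estimated with the improved Poisson regression". I read this as Poisson regression with robust variance, giving a risk ratio between arms. The sentence does not single out the primary outcome, and no other safety analysis is named. Covariate adjustment is stated for efficacy only, so I take the adverse event ratio as unadjusted.

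Under Sample Size Estimation: "We therefore set our recruitment goal to 20 patients per group in the present study". The basis is two rules of thumb for pilot studies, and the section says that no earlier data are available. It adds: "The results of this study will be used to determine the safety and feasibility of RICE". The same sentence goes on to say that the results will serve sample size and power calculations for phase 2.

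**The concern.** One sentence applies one method to two quite different outcomes. A favourable or poor mRS at 90 days will probably occur often enough in both arms to support a ratio. Serious events attributed to the intervention or to exercise may not. A ratio of two proportions needs at least one event in each arm, and with 20 patients per arm that is far from assured if such events are rare.

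The method is stated and it is attached to the primary outcome, so the question is its suitability rather than missing detail. At stake is the planned between-arm result for that outcome.

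**Working it through.** **Inputs.** n = 20 per arm, from Study Design ("at a ratio of 1:1, with 20 patients in each group"). The analysis set is all randomised patients, with no dropout allowance stated, so 20 per arm is used. The event rate p is not given; I assume 1% to 20%, equal in both arms unless noted.

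The 20 per arm cannot be re-derived by formula, because no rate, margin or precision is stated. It agrees with the two quoted rules: "10–20 patients in each group are sufficient to assess the feasibility of a pilot study" and "15 patients in each group are usually enough to decide whether a larger multicenter trial should be conducted".

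**Step 1: chance that the ratio has no finite, non-zero value.**

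P(no event in one arm) = q = (1 − p)^20

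P(at least one arm without events) = 1 − (1 − q)²

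P(both arms without events) = q²

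| Assumed p | q | At least one arm zero | Both zero |
|---|---|---|---|
| 1% | 0.818 | 96.7% | 66.9% |
| 2% | 0.668 | 89.0% | 44.6% |
| 5% | 0.358 | 58.8% | 12.9% |
| 10% | 0.122 | 22.8% | 1.5% |
| 15% | 0.039 | 7.6% | 0.15% |
| 20% | 0.012 | 2.3% | 0.01% |

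Setting 1 − (1 − q)² = 0.5 gives q = 0.293 and p = 1 − 0.293^(1/20) = 0.060. Below about 6% per arm, failure is more likely than not.

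Unequal rates do not remove the problem, because a low rate in one arm is enough. At 10% v 2% the chance is 1 − 0.878 × 0.332 = 71%. At 10% v 1% it is 1 − 0.878 × 0.182 = 84%.

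**Step 2: what the model does with such data.** Test fits of a robust-variance Poisson model were run in a general statistics package (not SAS, which the plan names). With 1 v 0 and 2 v 0 events, the log ratio ran off to about 20 with a meaningless standard error, although the software reported convergence. With 0 v 0 the fit failed.

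**Step 3: what the ratio says when it exists.** With a and b events, SE of the log ratio = √(1/a − 1/20 + 1/b − 1/20).

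- 1 v 1: ratio 1.0 (95% interval 0.07 to 14.9)
- 2 v 1: ratio 2.0 (0.20 to 20.3)
- 4 v 2: ratio 2.0 (0.41 to 9.7)

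**Step 4: what exact per-arm intervals give.** Clopper–Pearson, two-sided 95%:

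- 0/20: upper limit 1 − 0.025^(1/20) = 16.8%
- 1/20: 0.1% to 24.9%
- 2/20: 1.2% to 31.7%
- 3/20: 3.2% to 37.9%

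These exist for every possible count. An exact between-arm test can also be computed when one arm is empty, but it is weak: Fisher's test needs 5 v 0 for p < 0.05 (p = 0.047; 4 v 0 gives p = 0.106). It can therefore only be supportive.

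**The case against.** **The event rate is unknown.** This stands. At 10% per arm the ratio exists in 77% of trials, and at 15% to 20% in 92% to 98%. That serious related events are rare is plausible, but it is an assumption, and the point is conditional on it.

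**The sentence covers all adverse events, not only the primary outcome.** This stands in part. The commoner events listed under Primary Outcome may well support a ratio, and modified Poisson can stay for those. But no other safety method is named, so it does reach serious related events.

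**The trial would still have a primary result.** This stands. A reader might infer that the trial could end with no primary estimate at all. The Abstract speaks of incidence, which can be computed in each arm even with zero events. Only the between-arm ratio is lost.

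**A null ratio would be taken as proof of safety.** A reader might infer this from the statement that the results will determine safety. The article nowhere says that a non-significant ratio will be read that way. It describes a phase 1 safety and feasibility trial that also feeds phase 2 planning.

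**The ratio interval over-covers with sparse data.** It does, but that is no argument for the change. Clopper–Pearson is conservative too: with n = 20 its coverage is about 99.3% at a 2% rate, 98.4% at 5% and 98.9% at 10%. The reason to prefer it here is that it always exists.

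**An analysis plan not shown may handle sparse data.** It may. For that reason the absence of a precision statement under Sample Size Estimation is not counted as a fault here. What remains is that the article names a method unsuited to rare events.

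**Conclusion.** The concern holds in a conditional form. As written, the between-arm estimate for the primary outcome has no usable value whenever an arm of 20 has no serious related events. Assuming equal rates, the chance is 89% at 2% per arm, 59% at 5%, 23% at 10% and about 2% at 20%, and it exceeds one half below about 6%. This rests on an assumed event rate, 20 analysed patients per arm, an unadjusted ratio, and the reading of the named method as robust-variance Poisson.

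It does not show that 20 per arm is wrong for a pilot, that per-arm incidence is unavailable, or that the ratio is unsuitable for mRS or for commoner adverse events. It should be fixed before analysis, but it is not a fatal flaw.

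**What to change.** 1. For serious RIC-related and exercise-related adverse events, make the main analysis the number and proportion of patients with at least one event in each arm, with Clopper–Pearson 95% intervals.
2. Add an exact between-arm comparison as supportive, for example a risk difference with an exact interval.
3. Keep modified Poisson for mRS 0–2 versus 3–6, and for commoner adverse events where both arms have enough events to estimate it. Fix that condition before unblinding.
4. Word the safety conclusion as the rate excluded. With 0/20 in the RICE arm, for example, rates up to 16.8% are not excluded (two-sided 95%).

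The cost is a little more analysis work, and a stated precision that looks less favourable. No extra patients or data are needed.

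### Baseline infarct volume is measured but not named as a covariate for day-12 infarct volume, and the dependent variable is not stated: an avoidable loss of precision in a secondary outcome

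*Protocol article*

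**What the plan says.** Infarct volume on diffusion-weighted MRI is one of the two classes of secondary outcome in the Protocol article. Study Design schedules both scans: "Brain imaging with MRI will be performed on the day of the stroke for a baseline and again at 12 days". Secondary Outcomes adds: "The calculations will be performed by personnel blinded to clinical data and randomization at baseline and at day 12 ± 2".

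Statistical Analysis gives the model: "Infarct volume and β coefficient of the NIHSS score will be estimated by multiple linear regressions". It then gives one covariate list for efficacy in general: "Efficacy assessment will be adjusted based on age, gender, NIHSS baseline score, baseline condition, stroke subtype, intravenous alteplase treatment, and mechanical thrombectomy".

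The list names the baseline value of the NIHSS but not that of infarct volume. *Baseline condition* is not defined anywhere in the article. Nor does the section say whether the dependent variable is day-12 volume or change from baseline.

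Study Design allocates patients "at a ratio of 1:1, with 20 patients in each group". Sample Size Estimation sets that number by precedent from pilot studies, without an effect size, SD or power. The Randomization section mentions no stratification.

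**The concern.** The baseline value of a continuous outcome is the usual first covariate in its regression. Here it is already scheduled and read blind, yet the list that governs the model does not name it. In a 40-patient trial that admits thrombolysed, thrombectomy and untreated patients, baseline volumes may well differ between arms by chance. Baseline NIHSS can absorb only the part of that difference that it shares with volume.

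What is at stake is the width of the confidence interval for a secondary efficacy outcome. Sample Size Estimation also says that the results will feed the phase 2 power calculations. If phase 2 used infarct volume, an unnecessarily large residual SD could carry over.

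The article may leave many details to a fuller document, but it does commit to a covariate list. The point concerns what that list fixes.

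**Working it through.** **Inputs from the article.** 20 per arm, 40 in total; volume at baseline and day 12 ± 2; seven listed adjustment items; significance level 0.05 (two-sided assumed). The 20 per arm cannot be reproduced by a formula, because none lies behind it.

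**Assumed inputs.** ρ is the partial correlation of baseline with day-12 volume, given the other covariates. The documents give no value, so a range is used. About 9 degrees of freedom are taken as used by the listed covariates, since some have several categories.

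**1. Chance imbalance.** The SD of the difference in mean baseline volume is √(2/20) = 0.316 baseline SD. On a normal approximation, the chance that the difference exceeds 0.3 SD in either direction is 34%, and that it exceeds 0.5 SD is 11%.

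**2. Precision gained by adding baseline volume.** The SE ratio is √(1 − ρ²). Spending one more degree of freedom multiplies it by √[(40−2−9−1)/(40−2−9−2)] = √(28/27) = 1.018. The equivalent sample per arm without adjustment is 20/(1 − ρ²). Power is for a difference of 0.5 residual SD, by normal approximation; without baseline volume it is 35.2%. The last two columns ignore the lost degree of freedom.

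| ρ | √(1−ρ²) | SE ratio, df loss included | SE reduction | Equivalent n per arm | Power |
|---|---|---|---|---|---|
| 0.2 | 0.980 | 0.998 | about 0% | 21 | 36.5% |
| 0.3 | 0.954 | 0.971 | 3% | 22 | 38.1% |
| 0.5 | 0.866 | 0.882 | 12% | 27 | 44.7% |
| 0.7 | 0.714 | 0.727 | 27% | 39 | 60.0% |
| 0.9 | 0.436 | 0.444 | 56% | 105 | 95.2% |

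At ρ = 0 the lost degree of freedom costs about 2% of the SE.

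**3. Does baseline NIHSS already do the job?** A simulation (4,000 runs, 20 per arm, true difference 0.5 SD) had NIHSS and six unrelated covariates in the model. NIHSS was assumed to correlate 0.5 with both volumes. The raw correlation r between volumes then gives a partial correlation of (r − 0.25)/0.75.

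| r | Partial correlation | SD of estimate, without → with baseline volume | Power |
|---|---|---|---|
| 0.5 | 0.33 | 0.297 → 0.285 | 36% → 38% |
| 0.7 | 0.60 | 0.309 → 0.251 | 36% → 50% |
| 0.9 | 0.87 | 0.307 → 0.154 | 36% → 89% |

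So NIHSS is not a substitute when the two volumes correlate at 0.7 or more. At 0.5 little is lost.

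**4. If the outcome were change.** With equal variances at the two times (assumed) and no other covariates, the variance factor is 2(1 − ρ) for change and 1 − ρ² for day-12 volume adjusted for baseline. The difference is 2(1 − ρ) − (1 − ρ²) = (1 − ρ)², which is never negative. At correlations of 0.7, 0.8 and 0.9 the factors are 0.60, 0.40 and 0.20 for change, against 0.51, 0.36 and 0.19. At 0.5 they are 1.00 and 0.75.

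**The case against.** The best reply is that the text does not show baseline volume to be absent from the analysis. *Baseline condition* might be meant to cover it. The outcome might also be change: the abstract speaks of improvements in a list that includes infarct volume at 12 ± 2 days. If change is analysed, baseline volume is already used, and step 4 shows that most of the loss disappears at high correlations. This stands as a limit: a reader might infer that baseline volume has been excluded, but the documents support only that it is not named. It does not remove the point. NIHSS is listed separately from *baseline condition*, so that term does not plainly mean infarct volume, and a change score is never more precise than baseline adjustment.

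Other stronger readings also go beyond the documents:

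- **Raw scale.** A reader might infer that volume is analysed untransformed and that a few large infarcts would dominate. The article names linear regression and gives no scale; that detail may sit in a document not shown.
- **Strongest predictor.** This is plausible for two measurements of the same lesion, but the article gives no correlation. Showing only 0.7 to 0.9 would flatter the case.
- **Bias.** Under randomisation the estimator is not systematically biased by the omission. Chance imbalance is part of the sampling variation that its standard error reflects.
- **Size of the shift.** At a correlation of 0.8, a one-SD chance imbalance shifts the day-12 difference by 0.316 × 0.8 = 0.25 SD in an unadjusted comparison. The planned analysis is adjusted. If the listed covariates explain 25% of the variance, and the model with baseline volume 64%, the figure is √[(0.64 − 0.25) × 0.1] = 0.20 SD.

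Finally, this is a secondary outcome in a phase 1 safety and feasibility trial with no power target, so no stated power is lost.

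**Conclusion.** The point holds as a free improvement to a secondary analysis. The covariate list does not name a baseline measurement that the trial already collects, and the dependent variable is left open. If the model is fitted as listed, it gives up precision and leaves chance baseline imbalance in the estimate.

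The size depends wholly on an assumed partial correlation: negligible at 0.2 or 0.3, moderate at 0.5, and substantial at 0.7 and above. It also depends on day-12 volume being the outcome. With change as the outcome, the further gain is small at high correlations and larger at low ones. Nothing here touches the primary safety outcome or shows the treatment estimate to be biased.

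**What to change.** In Statistical Analysis, state that the dependent variable is day-12 infarct volume. Add baseline infarct volume as a covariate in its linear regression, on the same prespecified scale as the outcome (transformed if skewed). State that *baseline condition* means this measurement, or delete the term.

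No extra scan, visit or reading is needed. The only cost is one degree of freedom in a 40-patient model, about 2% of the standard error if baseline volume turned out to carry no information.
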